**Implementation**

During thirty months, after approval of this addendum and informed consent from the participants, additional blood draws will be performed at the same day as the ultrasound visits for the Predict study around 11, 22-24 and 30-32 weeks of gestation and during delivery if the delivery takes place at the Erasmus MC. This blood draw at 11 weeks of gestation will be combined with the current blood draw in

first trimester which is already being performed within the Predict study. Two extra tubes of blood will be collected in CellSave tubes and processed into plasma to be stored at -80°C until isolation of cfDNA takes place.

Our primary outcome are differentially methylated regions (DMRs) found in these cfDNA methylation profiles between uncomplicated controls versus women who develop pregnancy related diseases like pre-eclampsia, intra-uterine growth restriction and pre-term birth. It is not possible to make a power calculation beforehand because it is not known what the methylation profiles will look like. However, based on previous experiments to generate reference profiles using MeD-seq, the number of reliable DMRs stabilizes when having a sample size of  $\pm 8-9$  samples. The incidence of the above mentioned pregnancy related diseases in Europa are 4-5% for pre-eclampsia (27), 9% for preterm birth (28) and 8-10% for intra-uterine growth restriction (29). We aim to include 10 pre-eclampsia cases and account for 20-25% loss to follow up, including loss because of miscarriages. Therefore we intend to include 300 women in total. Because of the higher incidence of preterm birth and intra-uterine growth restriction it is likely this cohort will comprise at least 10 women affected by these complications as well.

We will identify specific DMRs in cfDNA from maternal plasma determined using MeD-seq and perform pathway analyses of genes associated with identified DMRs involved in associated diseases using <http://geneontology.org> in collaborations with the department of Developmental Biology, [name], Erasmus MC.

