## 1. Introduction and rationale

Impaired placenta development is involved in the causality of important obstetric complications, including preeclampsia and intrauterine growth restriction, resulting in increased maternal and fetal morbidity and mortality.(1, 2) DNA methylation is an important epigenetic mechanism involved in the (re)programming of gene expression and plays a vital role in placental development.(3-5)

Emerging evidence indicates a role for DNA methylation in the development of different placental related complications, either as cause or consequence. We and others have shown DNA methylation differences in postpartum placental tissues between pregnancies complicated by different placental related diseases, including preeclampsia, intra-uterine growth restriction and preterm birth as compared to controls.(6-13) For example, using the Illumina HumanMethylation450K beadchip technology Herzog *et al.* identified 869 differentially methylated positions in postpartum placental tissues between pregnancies diagnosed with preeclampsia <34 weeks of gestation compared to preterm birth controls.(12) DNA methylation differences associated with placental related complications could provide more insight in underlying pathophysiology. Moreover, disease-specific DNA methylation differences could potentially serve as biomarkers, ideally able to predict the risk of associated diseases at an early stage when targeted preventative interventions are most effective.(14)

Previous DNA methylation studies mainly focussed on postpartum placental tissues. (6-13) However, cfDNA originating from turnover of placental cell types circulates in maternal plasma providing the exciting opportunity to study placental DNA methylation in a non-invasive manner already during pregnancy.(15) cfDNA is currently already widely used for non-invasive prenatal testing of aneuploidies.(15) Between April 2017 and April 2023, all pregnant women in the Netherlands were offered NIPT on a trial basis (TRIDENT-2 study) and the NIPT uptake increased to over 40% in 2018.(16, 17) At the Erasmus MC, residual NIPT samples collected in the last two years are stored at the department of clinical genetics. Last month, promising results were reported by others who also used residual NIPT samples, indicative of cfDNA methylome profiling as promising tool for the prediction of early onset preeclampsia which could improve future obstetric care.(18)

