#### 4. Study population

##### 4.1 Population (base)

Eligible women participated in the TRIDENT-2 study and during the same pregnancy participated in the Predict study and/or delivered at the Erasmus MC Rotterdam.

Women who developed preeclampsia, intrauterine growth restriction or spontaneous preterm birth will be included and compared to controls with an uncomplicated pregnancy. We aim to include samples from twenty women per group (total n=80).

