##### 4.4 Sample size calculation

A power calculation beforehand is not possible because it is unknown how many and which methylation profiles will be identified. However, based on previous experiments to generate reference profiles using MeD-seq, the number of reliable DMRs stabilizes with a sample size of minimal 10 individuals as a consequence of filtering out SNPs and other genomic variation that in <10 samples might still be picked up as DMR. Therefore, in this

pilot study we include twenty patients per group, ten as training dataset and 10 patients for internal validation.

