## 5. Methods

### 5.1 *Please describe how you do conduct research and which methods are used, e.g. questionnaires, human material collection, extraction of data from medical records, analysis of images, the use of an app/medical device/diagnostic test, clinical tests to be performed, etc. Include information on frequency, duration, volumes, if a Data Management Plan is available (then please upload DMP).*

This study will use data previously collected in the Predict study, medical records, and blood samples previously collected for NIPT in the TRIDENT-2 study. Participation in the TRIDENT-2 study will be checked for Predict participants and for eligible patients who had complicated deliveries at the Erasmus MC Rotterdam in the last two years in collaboration with the Clinical Genetics Department at the Erasmus MC. Cases and controls will be selected until twenty patients in each group are selected. The MeD-seq technology will be used to investigate DNA methylation profiles in cfDNA between women who developed preeclampsia, intrauterine growth restriction or spontaneous preterm birth compared to uncomplicated control pregnancies. Custom Python scripts will be used to process the acquired DNA methylation profiles. Raw data files (fastq) will be filtered to be able to distinguish methylation data from background data and will be mapped to the human genome (hg38) using bowtie. To subsequently analyse DMRs, we will generate both regional (promoter, gene body and CpG Island regions) as genome-wide methylation scores. For the genome wide analysis, a sliding window technique will be used to detect DMRs. The Chi-squared test will be used for statistical testing with either the False Discovery Rate (FDR) or Bonferroni correction for multiple testing. A FDR or Bonferroni adjusted p-value <0.05 will be considered significant. After DMRs are determined, Z-score transformation of the read count data will be applied for unsupervised hierarchical clustering analysis. Pathway analyses will be performed using <http://geneontology.org>.

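### Sub-study 3 fills each group to a quota of twenty without fixing a selection order or matching on NIPT draw date, so draw date and storage time can become tied to disease group

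*Protocol*

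**What the plan says.** Sub-study 3 compares three case groups (pre-eclampsia, growth restriction, spontaneous preterm birth) with one uncomplicated group, twenty women each and 80 in total (sections 4.1 and 4.2). The selection rule in section 5.1 is: "Cases and controls will be selected until twenty patients in each group are selected". Section 4.3 has no exclusion criteria.

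On where women are looked for, section 5.1 states: "Participation in the TRIDENT-2 study will be checked for Predict participants and for eligible patients who had complicated deliveries at the Erasmus MC Rotterdam". Read literally, hospital deliveries outside Predict are searched for cases only. Sections 4.1 and 4.2 are wider and admit any woman who took part in Predict or delivered at the centre.

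On the archive, section 1 says that at the centre "residual NIPT samples collected in the last two years are stored at the department of clinical genetics", and that TRIDENT-2 ended in April 2023. Each group of twenty is split: "ten as training dataset and 10 patients for internal validation" (section 4.4). Sections 7 and 11.3 describe linking a sample to its own patient. That is not matching of controls to cases.

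**The concern.** A rule that stops at twenty, run separately in four groups, says when to stop but not which women to take. If a list is worked through in date or study-number order, a group with many candidates closes quickly and takes its samples from a short stretch of the archive. A group with few candidates goes on longer and reaches further through it. Case and control plasma would then differ in draw date, time in storage and period of routine NIPT processing.

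Any effect of these on measured methylation would be indistinguishable from a disease effect. The internal validation offers no protection: the ten training and ten validation women in a group come out of the same selection, so an artefact found in one half would be expected in the other. If case and control dates barely overlap, later adjustment cannot separate date from disease. The choice therefore belongs in the design and cannot be left to an analysis plan.

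**Working it through.** **The plan's own figure.** 4 groups × 20 = 80, and 10 + 10 = 20 per group. Both reproduce. There is no power calculation to check.

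**Inputs**
- Incidences, from the Implementation section of Addendum 3 (sub-study 1): pre-eclampsia 4–5%, preterm birth 9%, growth restriction 8–10%. Using them in sub-study 3 is an assumption. They are European population figures, and sub-study 3 takes only spontaneous preterm birth.
- Usable archive: two years back from the version date (29 September 2023), ending in April 2023, so about 18–19 months.
- Eligible women per month (M): not given, so varied from 25 to 200.
- Predict inflow: about 10 women per month, assumed from sub-study 1 (300 women in 30 months).
- NIPT uptake: 40% (section 1 says over 40% in 2018).
- Hospital deliveries per month, and a pre-eclampsia share of 15% at a referral hospital: assumptions.

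**Relative frequency.** Uncomplicated share ≈ 1 − 0.045 − 0.09 − 0.09 = 0.775. Ratio to pre-eclampsia: 0.775/0.045 = 17.2. Over the stated ranges it runs from 0.76/0.05 = 15.2 to 0.79/0.04 = 19.75. The share is rough, because it ignores overlap between the three diagnoses and all other complications.

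**Case A: one common pool, filled in date order.** With λ candidates per month, the twentieth is expected at 20/λ months, and the mean draw date of the first twenty is 10.5/λ. Here λ = 0.045M for pre-eclampsia and 0.775M for controls.

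| M per month | Months to 20 PE | Months to 20 controls | Mean gap = 10.5/(0.045M) − 10.5/(0.775M) |
|---|---|---|---|
| 25 | 17.8 | 1.0 | 9.3 − 0.5 = 8.8 |
| 50 | 8.9 | 0.5 | 4.7 − 0.3 = 4.4 |
| 100 | 4.4 | 0.3 | 2.3 − 0.1 = 2.2 |
| 200 | 2.2 | 0.1 | 1.2 − 0.1 = 1.1 |

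Simulation with a finite archive (1,500 runs per setting) agrees. At M = 25 the gap is 7.9 months for an 18-month archive and 8.6 for 24 months; the other rows give 4.3–4.4, 2.2 and 1.1. Draw date alone separates pre-eclampsia from controls with an AUC of 0.97 in these settings. With a 15% pre-eclampsia share and M = 50, the gap is 1.1 months and the AUC 0.88.

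**Case B: pools as section 5.1 describes them, each filled in date order.** Controls come from Predict only: 10 × 0.40 × 0.775 = 3.1 per month, so 20/3.1 = 6.5 months to fill and a mean date of 10.5/3.1 = 3.4 months. Pre-eclampsia cases come from hospital deliveries (the few Predict cases are ignored):

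| Deliveries per month, PE share | PE per month | Months to 20 | Mean gap, cases minus controls |
|---|---|---|---|
| 50, 4.5% | 50 × 0.4 × 0.045 = 0.9 | 22.2 (beyond the archive) | – |
| 100, 4.5% | 1.8 | 11.1 | 5.8 − 3.4 = +2.4 |
| 200, 4.5% | 3.6 | 5.6 | 2.9 − 3.4 = −0.5 |
| 100, 15% | 6.0 | 3.3 | 1.75 − 3.4 ≈ −1.6 |

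The sign changes within plausible inputs.

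**Case C: the same quotas, drawn at random from the full list of one pool.** Simulated mean gap −0.13 to +0.06 months, AUC 0.49–0.50, with controls spanning about 16 of 18 or 22 of 24 months.

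**What a gap could do (illustration only).** The documents give no drift size. Suppose 0.05 woman-level SD per month. An 8-month gap shifts the means by 8 × 0.05 = 0.4 SD. With 10 per group the standard error is √(2/10) = 0.447, and the chance of an unadjusted two-sided p < 0.05 in a null region is Φ(0.4/0.447 − 1.96) + Φ(−0.4/0.447 − 1.96) = 14.5%. For a 2-month gap it is 5.6%. This is a comparison of woman-level means, not the planned chi-squared test, so it does not estimate this study's error rate.

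**The case against.** The strongest reply is that the protocol nowhere says women are screened in date order. That is right. A reader might infer from the quota sentence that controls must come from a narrow window while pre-eclampsia cases span the whole archive. The document does not support this. It would need date-order filling, a single shared pool and a small monthly inflow, and none of these is stated. The quota is harmless if the twenty are drawn at random (Case C).

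A reader might also infer that the distortion is greatest for the rarest disease. Case B shows that this does not follow once controls come only from Predict.

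Nor is the effect of storage or processing period on these samples documented, so no error rate can be claimed.

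A further reply is that sub-study 3 is a pilot, to be set beside the prospective Predict subcohort, where an artefact of the NIPT archive would have no reason to recur. This limits the long-run harm. It does not protect sub-study 3's own DMR list or its pathway analysis (objectives 1 and 2). It also weakens objective 3, because a validation cohort with its own artefacts makes agreement or disagreement hard to interpret.

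What remains is that nothing in the plan prevents the imbalance, and the internal validation cannot detect it.

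**Conclusion.** The concern holds in conditional form. Section 5.1 leaves open which eligible women are taken and protects neither draw date nor storage time. If the groups are filled in date or study-number order, draw dates will differ between cases and controls unless fill times happen to agree. In a common pool at the borrowed incidences, the mean gap for pre-eclampsia is about 1 month at 200 eligible women per month and 8–9 months at 25. With Predict-only controls it can shrink or reverse. These figures rest on assumed pool sizes, incidences from sub-study 1 and an assumed Predict inflow. Whether any gap would produce false DMRs depends on a storage or processing effect that the document does not quantify. The point is worth settling before samples are picked, because it cannot be reliably repaired afterwards.

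**What to change.** Replace the quota sentence in section 5.1 with a selection procedure:

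1. List all eligible women with a stored TRIDENT-2 sample and consent for residual use, with NIPT draw date, before anyone is selected.
2. Take the cases. Where a case group has more than twenty candidates, draw twenty at random.
3. Draw the twenty controls at random within quarter of NIPT draw date, frequency-matched to the cases. One control group serves three comparisons, so state that the target is the quarter distribution of the three case groups together.
4. Balance draw quarter between the training and validation halves of each group.

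Section 5.1 should also be reconciled with 4.1 and 4.2 on whether uncomplicated hospital deliveries outside Predict may serve as controls, since this sets the length of the control list.

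The cost is that the full candidate list must be compiled first, where the present rule lets the search stop at twenty. The total stays at 80, with no extra samples or sequencing. Even with Predict-only controls the list should suffice: at the assumed 3.1 per month, 18–19 months give 3.1 × 18 = 56 to 3.1 × 19 = 59 candidates for twenty places, before any loss for missing consent or samples.

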## 5. Methods

- 5.1 *Please describe how you do conduct research and which methods are used, e.g. questionnaires, human material collection, extraction of data from medical records, analysis of images, the use of an app/medical device/diagnostic test, clinical tests to be performed, etc. Include information on frequency, duration, volumes, if a Data Management Plan is available (then please upload DMP).*

Placenta samples from all three trimesters from both complicated and uncomplicated pregnancies will be obtained in multiple ways as described earlier: via the Fetal Biobank Amsterdam (retrospectively), abortion clinics (prospectively) and the Erasmus MC (both retrospectively and prospectively). After sample collection, DNA will be isolated from placental biopsies. MeD-seq technology will be used to investigate DNA methylation profiles between different trimesters in both complicated and uncomplicated pregnancies. Custom Python scripts will be used to process the acquired DNA methylation profiles. Raw data files (fastq) will be filtered to be able to distinguish methylation data from background data and will be mapped to the human genome (hg38) using bowtie. To subsequently analyse DMRs, we will generate both regional (promoter, gene body and cytosine-phosphate-guanine (CpG) Island regions) as genome-wide methylation scores. For the genome-wide analysis, a sliding window technique will be used to detect DMRs. The Chi-squared test will be used for statistical testing with either the False Discovery Rate (FDR) or Bonferroni correction for multiple testing. A FDR or Bonferroni adjusted p-value <0.05 will be considered significant. After DMRs are determined, Z-score transformation of the read count data will be applied for unsupervised hierarchical clustering analysis. Pathway analyses will be performed using <http://geneontology.org>.

- 5.2 *Standard clinical care versus extra for research:  
Indicate which of the methods are part of standard clinical care and which tests and/or visits are extra for research purposes i.e. not standard clinical care.*

Since only residual tissues will be used, participants will not undergo any additional procedures. The placentas would otherwise be discarded. Sample collection and MeD-seq is only for research purposes.

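### Sub-studies 2 and 3 scan the whole genome without handling fetal sex, so a chance sex imbalance between groups of about 10 can yield Y-region (and, in placental tissue, X-region) DMRs; the exposure is mainly in sub-study 2

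*Protocol*

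**What the plan says.** Section 5.1 (Methods) of sub-studies 2 and 3 describes nearly the same pipeline. Reads are filtered and, in sub-study 3, "will be mapped to the human genome (hg38) using bowtie". Next, "we will generate both regional (promoter, gene body and CpG Island regions) as genome-wide methylation scores". The scan follows: in sub-study 3, "For the genome wide analysis, a sliding window technique will be used to detect DMRs", and in sub-study 2, "For the genome-wide analysis, a sliding window technique will be used to detect DMRs". On testing: "The Chi-squared test will be used for statistical testing with either the False Discovery Rate (FDR) or Bonferroni correction for multiple testing", with the threshold "A FDR or Bonferroni adjusted p-value <0.05 will be considered significant". After that, "Z-score transformation of the read count data will be applied for unsupervised hierarchical clustering analysis", and the genes linked to the DMRs go to pathway analysis.

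On selection, sub-study 3 says "Cases and controls will be selected until twenty patients in each group are selected". Its section 4.3 lists no exclusions, and section 4.4 splits each group of twenty into ten for training and ten for internal validation. It justifies ten on the ground that SNPs and other genomic variation are filtered out at that size. Sub-study 2, section 4.4, aims for at least 10 samples per trimester and states no validation set.

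Fetal sex and the sex chromosomes are not mentioned in any of the three sub-study protocols. The text neither says that X and Y are tested nor says that they are left out.

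**The concern.** Y-chromosome reads come only from male fetuses or placentas. X dosage and X-inactivation methylation also differ by sex. If one group holds more males than another, read counts on Y, and in placental tissue on X, differ between the groups for a reason unrelated to trimester or disease. Multiplicity correction does not target this, because the difference between the samples is real. It only sets how large the difference must be before it is declared.

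The protocol's own safeguard does not cover it either. Ten samples may filter out a rare variant that happens to cluster in one group. They cannot filter out a trait present in about half of all samples.

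The DMR list is the primary endpoint of both sub-studies and feeds the clustering and the pathway step. Y regions move together, so one imbalance can add a block of correlated regions and pull the clustering towards sex. In sub-study 2 the profiles are also meant to help separate the placental from the maternal fraction of cfDNA in later work, so sex-linked regions could enter that reference.

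**Working it through.** **Plan's own figure.** Sub-study 3: 4 groups × (10 + 10) = 80, as stated in section 4.1. Both sub-studies declare a power calculation impossible, so there is no power figure to reproduce.

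**Inputs.** From the protocol: 10 per group (sub-study 2, section 4.4; training and validation sets in sub-study 3, section 4.4); placental share of cfDNA 13%, range 3–30% (sub-study 2, section 1). Assumed, because the protocol gives none of them: probability of a male 0.5; Chi-squared test on read counts pooled within group, Poisson reads, equal sequencing totals; 2 to 100 reads per male sample in a Y region; 20,000 or 100,000 tests.

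**Step 1: imbalance.** Male counts are two independent Binomial(10, 0.5) variables; the difference is exact by convolution.

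| Difference in males, 10 v 10 | Probability |
|---|---|
| at least 1 | 82.4% |
| at least 2 | 50.3% |
| at least 3 | 26.3% |
| at least 4 | 11.5% |

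A male probability of 0.512 changes these by less than 0.1 percentage point. At least one of the three trimester pairs is off by 2 or more in 78% (sub-study 2); at least one of three case groups against the shared controls in 84% (sub-study 3, one set of ten).

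**Step 2: worked Y regions.** With pooled counts a and b, z = (a − b)/√(a + b). Bonferroni over 20,000 tests needs p < 0.05/20,000 = 2.5e-6.

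| Males | Reads per male | a v b | p | Passes 2.5e-6? |
|---|---|---|---|---|
| 6 v 4 | 30 | 180 v 120 | 5.3e-4 | no |
| 6 v 4 | 100 | 600 v 400 | 2.5e-10 | yes |
| 7 v 3 | 30 | 210 v 90 | 4.3e-12 | yes |

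**Step 3: sub-study 2, one Y region.** Simulated chance that at least one of the three trimester pairs is significant, 10 per trimester:

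| Reads per male | 20,000 tests | 100,000 tests |
|---|---|---|
| 5 | 3% | 2% |
| 10 | 14% | 10% |
| 20 | 34% | 29% |
| 30 | 48% | 43% |
| 100 | 79% | 77% |

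For an X CpG-island region in tissue, taking the male signal as 5% of the female signal, a single comparison is significant in 0.4% (5 reads per female) to 11% (20 reads), Bonferroni over 100,000.

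**Step 4: sub-study 3.**
- Validation. A difference of at least 2 males in one direction has probability 0.5034/2 = 0.2517, so the same direction in both sets of ten has 2 × 0.2517² = 12.7%, down from 50.3%. For at least 3 males it is 3.5%, down from 26.3%. For any of the three contrasts the figures are 30% and 9%.
- Dilution. If 30 and 100 are tissue depths, a 13% share leaves about 4 and 13 reads. Then 7 v 3 males gives 27.3 v 11.7 (p = 0.012) and 91 v 39 (p = 5e-6); neither passes 2.5e-6.
- One Y region, one contrast, Bonferroni over 100,000: under 0.1% (2 reads), 7% (13 reads), 49% (100 reads). Requiring validation as well: under 0.1%, 0.3%, 12%.
- X CpG islands, same correction: about 0% at a 13% share, at most 0.8% at 30%.

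**Step 5: if the test counts samples.** Presence or absence of Y in 10 v 10 reaches unadjusted p < 0.05 in 4.2% and almost never after correction (about 0.0002% over 1,000 tests).

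**The case against.** The strongest reply is that this rests on silence. No sentence says X and Y are tested, and a chromosome filter in the custom scripts, or in an analysis plan not shown here, would end the matter. That limits the claim: a reader might infer that X and Y certainly are tested and that sex-driven regions will be reported as disease- or trimester-specific, and the protocol does not support that. It does fix the neighbouring steps down to the aligner and the Z-score and describes the scan as genome-wide, so its plain reading includes X and Y.

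Read depth, number of tests and the unit of the Chi-squared test are not given, and a sample-level test would leave almost no risk. This stands too, although section 5.1 does speak of read count data for the clustering step.

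For sub-study 3, dilution and internal validation are real protection, and X is almost unaffected because every plasma donor is a woman. This is why the point lies mainly with sub-study 2.

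Two replies carry less weight. Ten per trimester is a minimum, but larger groups do not help under a pooled-read test. With n per group and m reads per male, Var(a − b) = nm + nm²/2 and E(a + b) = nm, so the variance of z is about 1 + m/2, whatever n is. And Y regions are indeed recognisable by location and removable later, but doing so after the results are seen changes the primary endpoint list post hoc.

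**Conclusion.** The point holds as a conditional one. Followed as written, section 5.1 lets a chance sex imbalance enter the DMR list, and an imbalance of 2 or more males is expected in about half of 10 v 10 comparisons. Whether it produces declared DMRs depends on a pooled-read test and on coverage. In sub-study 2, for one Y region and 20,000 tests, the chance ranges from 3% at 5 reads per male to 79% at 100; X regions in tissue add to this. In sub-study 3 the risk is much smaller, concerns Y almost only, and needs high Y coverage to survive validation.

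The figures assume a male probability of 0.5, Poisson reads, equal sequencing totals, and the stated depths and test counts. None of these comes from the protocol. The change is worth making for sub-study 2 and is less urgent for sub-study 3.

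**What to change.** In section 5.1 of sub-studies 2 and 3, state that the main DMR lists, the clustering and the pathway input use autosomes only, and that X and Y regions are analysed separately within fetal sex and labelled as such. Take fetal sex from the record or, for the anonymous biobank and abortion-clinic samples in sub-study 2, from Y-mapped reads.

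The cost is one filter in the existing scripts; sample sizes do not change. Sex-linked regions lose power, since strata would hold about 5 v 5, and X-linked placental signal moves out of the main list. Balancing selection on sex or adjusting for it in the test are alternatives. The autosome rule is the simplest to apply to samples already collected.

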### 1. Introduction and rationale

The developmental origins of health and disease (DOHaD) hypothesis is supported by accumulating evidence showing the importance of the gestational environment for fetal development as well as for health outcomes later in life (1-3). Epigenetic mechanisms, of which DNA methylation is the most studied, have been proposed to play a role in affecting developmental programming (1-3) and are essential for normal placental development and function (4, 5). Impaired placentation has been associated with multiple adverse pregnancy outcomes. We and others have shown differentially methylated regions (DMRs) in postpartum placentas in pregnancies affected by a range of obstetric complications, including preeclampsia, intra-uterine growth restriction and preterm birth. This indicates a role for epigenetic mechanisms in disease development, either as cause or consequence. (6-14)

Placental methylation profiles early and mid-gestation are largely understudied due to the impossibility to non-invasively investigate placental tissue during pregnancy. Previous studies using tissues from elective abortions showed that placental DNA methylation in general increases with advanced gestational age (15-17). A promising alternative to study placental DNA methylation noninvasively already during pregnancy is by use of so called cell free DNA (cfDNA) originating from turnover and spill of placental cell types into the maternal circulation. Currently, cfDNA is already widely used for non-invasive prenatal testing for chromosomal aneuploidies as part of prenatal screening.(18) However, on average only 13% (range 3-30%) of total cfDNA within the maternal circulation originates from the placenta (19), with the remaining cfDNA originating from maternal tissues, hampering specificity of selection and detection of placental DNA methylation.

From the different methods to study genome-wide DNA methylation we will use the recently developed MeD-seq technology which focusses on regional changes in DNA methylation, requiring less sequencing depth as compared to whole-genome bisulfite sequencing while providing a more extensive coverage of the genome as compared to most other techniques.(20, 21) Besides, MeD-seq requires a limited amount of input DNA and is therefore one of the few technologies compatible with the low cfDNA levels available in clinical practice.(22)

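### The Chi-squared test fixed for calling DMRs in sub-studies 2 and 3 has, if reads are pooled per group, no term for variation between women, so the adjusted 5% level would not hold

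*Protocol*

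**What the plan says.** Section 5.1 of both protocols describes the same pipeline. Reads are filtered and mapped, regional scores (promoter, gene body, CpG island) and genome-wide methylation scores are generated, and for the genome-wide part "a sliding window technique will be used to detect DMRs". Then: "The Chi-squared test will be used for statistical testing with either the False Discovery Rate (FDR) or Bonferroni correction for multiple testing". The threshold follows: "A FDR or Bonferroni adjusted p-value <0.05 will be considered significant". Read counts are named only at the next step, where "Z-score transformation of the read count data will be applied for unsupervised hierarchical clustering analysis".

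The DMR list is the main endpoint of both sub-studies (section 8.1 of each protocol). Sub-study 2 aims for at least 10 samples per trimester (4.4). In sub-study 3, section 4.4 says that in this "pilot study we include twenty patients per group, ten as training dataset and 10 patients for internal validation".

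The documents acknowledge variation between individuals in three places:
- Sub-study 3, section 4.4, justifies the minimum of ten by "filtering out SNPs and other genomic variation that in <10 samples might still be picked up as DMR".
- Sub-study 2, section 1, says that "on average only 13% (range 3-30%) of total cfDNA within the maternal circulation originates from the placenta".
- The introduction of Addendum 3 says that exercise and obesity alter cfDNA quantity and hence the placental fraction.

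Neither section 5.1 names a variance term for this. Addendum 3 names no test, so the point concerns sub-studies 2 and 3 only.

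**The concern.** The independent unit is the woman or the placenta, not the read. A Chi-squared test on reads summed over a group compares the group difference with Poisson noise alone. When women differ for reasons unrelated to group, the true variance of that difference is larger and the p-value is too small. FDR and Bonferroni procedures both take valid p-values as input and cannot repair invalid ones. Recruiting more women does not help either, because the inflation depends on reads per woman and not on the number of women.

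Clustering, pathway analysis and candidate biomarkers all follow from the DMR list, and sub-study 3 is also meant to serve as a validation cohort for the prospective subcohort. The test and threshold are written into the protocol, so this is not a detail left to an analysis plan.

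**Working it through.** **Inputs from the documents:** Chi-squared test and adjusted p < 0.05 (5.1 of both protocols); 10 training and 10 validation women per group (sub-study 3, 4.4).

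**Assumed, because the documents do not give them:** m reads per woman per region, between-woman coefficient of variation CV, and M = 20,000 null regions.

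**Step 1. Stated level.** With CV = 0 the pooled test does what is stated: simulated size is 0.049 to 0.051.

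**Step 2. Pooled reads with CV above 0.** A woman's count has variance m + m²CV² instead of m, so the variance inflation factor is VIF = 1 + m × CV².

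- True size at nominal 5% = 2 × [1 − Φ(1.960/√VIF)].
- The Bonferroni threshold is 0.05/20,000 = 2.5e-6, that is z = 4.708. Expected false calls = 20,000 × 2 × [1 − Φ(4.708/√VIF)].

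| m | CV | VIF | 1.960/√VIF | True size | 4.708/√VIF | False Bonferroni calls (target 0.05) |
|---|---|---|---|---|---|---|
| 10 | 0.1 | 1.1 | 1.869 | 6.2% | 4.489 | 0.14 |
| 10 | 0.2 | 1.4 | 1.656 | 9.8% | 3.979 | 1.4 |
| 20 | 0.3 | 2.8 | 1.171 | 24% | 2.814 | 98 |
| 50 | 0.3 | 5.5 | 0.836 | 40% | 2.008 | 894 |

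**Step 3. FDR instead of Bonferroni.** Gamma-Poisson simulation, 10 v 10, 20,000 null regions: Benjamini-Hochberg gave 0 to 4 false calls at m = 10 with CV 0.1 to 0.2, about 680 at m = 30 with CV 0.2, and about 4,900 at m = 30 with CV 0.35. With 20 women per group the size was unchanged.

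**Step 4. Effect of the split.** Validation in a second 10 v 10 was simulated with the same test (p < 0.05, same direction; the protocol states no criterion). Mean null regions passing training, then validation:
- m = 10, CV 0.2: 4.8, then 0.8
- m = 30, CV 0.2: 695, then 61
- m = 30, CV 0.35: 4,911, then 905

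**Step 5. The other reading: each woman classed as methylated or not.** At 10 v 10, perfect separation gives χ² = 20 and p = 7.7e-6. Since 0.05/7.744e-6 = 6,456, no region can pass Bonferroni when more than 6,456 are tested. With Benjamini-Hochberg among 20,000 regions, four perfectly separating regions do pass (0.05 × 4/20,000 = 1e-5). At 20 v 20 the maximum is χ² = 40, p = 2.5e-10, which also passes.

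**Step 6. Woman as unit on the same simulated data.** A t-test on per-woman square-root counts kept the size at 0.049 to 0.052 in every setting, with on average 0 to 0.6 false Benjamini-Hochberg calls when no region truly differed. With 200 true two-fold DMRs, m = 30 and CV 0.35, it found about 46 at 10 v 10 and about 191 at 20 v 20.

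Uneven sequencing depth and overlapping windows were not modelled.

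**The case against.** **The input is inferred.** Before the test, section 5.1 speaks of methylation scores; read counts appear only after it, and pooling over a group is stated nowhere. This stands, and the point is conditional on it. Pooled counts remain the most plausible input for a Chi-squared test on sequencing data.

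**The size is not known.** A reader might infer that the DMR list will be mostly false, or will reflect individual variation as much as trimester or disease. The documents do not support either statement. Reads per region, CV and number of regions are all assumed, and at low depth and low CV the excess is small. Steps 2 to 4 use null regions only, while sub-study 2 (section 1) cites evidence that placental methylation generally increases with gestational age. The 3-30% placental fraction suggests a high CV only for placenta-derived reads in plasma; it says nothing about variation between placental biopsies.

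**There is a safeguard.** Sub-study 3 has a ten-sample minimum against genomic variation and an internal validation set. Step 4 shows that the split removes most false calls in the settings shown. It does not restore the level if the same test is reused, and sub-study 2 has no such split.

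**The woman-as-unit reading is not ruled out.** A reader might infer that the plan fails whichever way the test is read. Step 5 shows a hard limit only for Bonferroni at 10 v 10; FDR, or all 20 v 20, can reach significance.

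**The choice of correction could be settled later.** An analysis plan could fix FDR or Bonferroni before the data are seen, and nothing says that the choice will follow the results. What stands is that the protocol leaves two very different error rates open.

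**Sub-study 3 is a pilot.** No clinical decision follows from it and the raw data can be reanalysed. That limits the harm but does not make the stated 5% correct.

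**Conclusion.** The concern holds, on condition that reads are pooled per group. The test fixed for the main endpoint of sub-studies 2 and 3 then lacks a between-woman or between-placenta variance term, and the adjusted p < 0.05 threshold does not deliver its stated error rate. The direction is certain whenever individuals differ, which the protocols say they do.

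The amount is not certain. With 20,000 null regions assumed, expected false Bonferroni calls range from 0.14 to 894 over the settings in step 2, against 0.05 intended. The documents do not allow a choice within that range. If the woman is in fact the unit, this inflation does not arise; the remaining problem is the Bonferroni ceiling of about 6,456 regions at 10 v 10.

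**What to change.** In section 5.1 of both protocols:

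- Replace the Chi-squared test by a per-sample analysis with the woman or placenta as unit. Options are a negative binomial or quasi-likelihood count model with a sequencing-depth offset, or a moderated t-test on normalised log counts.
- State what enters the test (counts or scores, per sample).
- Check calibration by permuting group labels and report the result.
- Name one multiplicity correction in advance, for example Benjamini-Hochberg at 5% for discovery.
- In sub-study 3, state the criterion by which a DMR counts as validated.

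The change needs wording and standard software, and no new samples or sequencing. Its cost is a shorter DMR list and an honest view of power: at 10 v 10, with m = 30 and CV 0.35, about 46 of 200 true two-fold DMRs were found, against about 191 at 20 v 20. The sponsor should therefore reconsider whether splitting sub-study 3 into 10 and 10 is still the best use of its samples.
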